### Outcome parameters

The primary end point of the study is:comparison of the results of the use of metallic and absorbable tacks to fix lightweight polypropylene meshes during LIVHR, in terms of hernia recurrence, to test the hypothesis of non-inferiority of absorbable tacks when compared to titanium tacks.

The endpoint will be measured by the recurrence rate at 3 years; interim evaluations will be done at 1-year and 2-year follow-up.

The secondary end point is:comparison of intraoperative and early post-operative outcomes, in terms of surgical complications, post-operative stay, comfort and pain

The comfort and pain parameters will be measured using the licensed CC S; surgical complications will be evaluated by the Clavien-Dindo classification [32] and on the basis of reoperation and readmission rates (1–2 and 3 years).

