## Methods/Design

### Trial design, locations and organizational structure

The TACS trial is a multicentric prospective randomized study. It will involve five surgical units having extensive experience in both metallic and absorbable tacks for LIVHR (this means that each surgeon participating in the study usually performs more than fifty procedures per year with the devices used in the study).

The Reference Center (General Surgery Unit, ICOT Hospital, Latina, Italy) will coordinate the study and handle the data analysis and interim evaluations.

The study will develop according to the *Helsinki Declaration*. It obtained the Ethical Committee approval (Independent Ethical Committee “Lazio 2”) on 26 May 2014 prior to registration (reference number asl_lt/15675/A001/2014)*.*

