### Intervention, preoperative and post-operative management

All patients will be assessed preoperatively by clinical examination and abdominal computed tomography (CT) or ultrasound (US) scan to evaluate the size and number of the defect(s).

The devices used in the study (meshes and tacks) will be:Physiomesh™ (Ethicon Endo-Surgery, Johnson & Johnson, Inc.), a lightweight polypropylene mesh with double face absorbable layer engineered to be placed on the peritoneal surfaceProtack™ (Covidien Surgical, Mansfield, MA, USA), permanent titanium helicoidal tacksSecurestrap™ (Ethicon Endo-Surgery, Johnson & Johnson, Inc.), “U”-shaped absorbable tacks made by polydioxanone, completely resorbed by hydrolysis within 12–18 months after implantation

All the procedures will be carried out using the same surgical technique, already described in previous studies [22,23]. In particular, there will be careful adhesiolysis of the entire abdominal wall, a search for additional defects, overlapping the defect for at least 3 cm on each side, setting the tacks at the distance of 1.5 cm in a double crown configuration [31] and no use of transfixed sutures or glue. After surgery, compressive dressing will be placed for 4 weeks.

Each surgeon will be provided with a precise description of the standardized technique and a checklist of the aforementioned necessary technical items to be controlled, filled for every patient and turned back to the Reference Center. Adherence to the protocol will be assessed by review of the procedure videos: all centers will share the videos with the Reference Center. The operations performed by the Reference Center will be examined by the primary surgeon of another participating center who will check that all items on the checklist have been correctly performed.

A member of the operating team will note the patients and intervention characteristics in an online database including the following parameters:Patient characteristics (sex, age, comorbidities, personal therapy)Hernia features (location and size)Mesh sizeType of tacks (absorbable/non-absorbable)Number of tacks usedOperating timePost-operative hospital stay

Post-operative complications during the index admission (according to the Clavien-Dindo classification) [32].

Acute post-operative pain (using the Visual Numeric Scale (VNS) for pain classification) [33].

Pain management (use of analgesic drugs).

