### Statistical methods

The sample size calculation is based on the primary end point. A sample size of 110 in each group permits the achievement of a study power of 80 %, to detect a non-inferiority margin difference between the devices used. The reference group proportion is 0.07. The treatment group proportion is assumed to be 0.13 under the null hypothesis of inferiority. The statistic test used will be the one-sided Z test (unpooled). The significance level of the test will be targeted at 0.05.

The same sample size will also be adequate to evaluate the secondary endpoints.

Statistical analysis will be performed at 1, 2 and 3 years after the first patient’s enrollment by a statistician affiliated with the Reference Center.

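### The 1- and 2-year evaluations of recurrence are not separated from the 3-year non-inferiority test; if its margin and level were used early, they would be too lenient

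*Protocol article*

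**What the plan says.** In the protocol article, Outcome parameters, the primary comparison is non-inferiority of absorbable to titanium tacks on recurrence: "The endpoint will be measured by the recurrence rate at 3 years". The same sentence continues that "interim evaluations will be done at 1-year and 2-year follow-up".

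Statistical methods bases the sample size on the primary endpoint. It names one test (one-sided, unpooled Z) and one level: "The significance level of the test will be targeted at 0.05". It gives one pair of proportions: "The reference group proportion is 0.07", with 0.13 for absorbable tacks under the null. The margin is therefore 0.13 − 0.07 = 0.06. The section then sets a calendar: "Statistical analysis will be performed at 1, 2 and 3 years after the first" patient is enrolled.

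Three other statements bear on the point:

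- Under Trial design, the Reference Center "will coordinate the study and handle the data analysis and interim evaluations". The intervention section shows that this center also operates on trial patients.
- The absorbable tacks are "completely resorbed by hydrolysis within" 12–18 months.
- Under Randomization, operating staff know the allocation. Patients do not, and post-operative checks are made by a blinded physician not directly involved in the study.

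**The concern.** A margin is tied to the time at which the rates are measured. Six points is the difference allowed once recurrence has reached 7 % with titanium. At 1 year only part of the 3-year recurrences have occurred, so both rates and their difference are smaller while the permitted difference stays at six points. A device that only just fails at 3 years can then look acceptable at 1 year. The 1-year look also comes before the absorbable tacks are fully resorbed, so it may miss any excess that follows loss of fixation.

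The early evaluations are attached to the primary endpoint, and the article supplies no other margin, level or purpose for them. A 1-year non-inferiority statement could thus be made by following the text, although it would say little about the 3-year question. The Discussion says that use of absorbable tacks could be encouraged if non-inferiority is shown, so an early claim could affect practice.

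A lesser concern is that interim results are produced within a center that operates on trial patients.

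**Working it through.** **Inputs.** From Statistical methods: 110 per arm, one-sided 0.05 (critical value 1.645), unpooled Z test, margin 0.06, rates 0.07 and 0.13 at the margin. The article gives no time course of recurrence and no accrual period, so both are assumptions here and are varied. The stated 80 % power is a separate matter and is not used.

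**Rule.** Non-inferiority is declared if (p_B − p_A − 0.06)/SE < −1.645, where SE = √{[p_A(1−p_A) + p_B(1−p_B)]/n}. With true difference δ, the pass probability is approximately Φ[(0.06 − δ)/SE − 1.645]. Exact values come from enumerating both binomial distributions.

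**Year 3, the plan's own level.** δ = 0.06 and SE = √[(0.0651 + 0.1131)/110] = 0.0402. Φ(−1.645) = 0.05; exact 0.055. The nominal level is reproduced, with slight excess.

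**Year 1, even spread.** The rates are one third of the 3-year values, 0.0233 and 0.0433, so δ = 0.02. SE = √[(0.0228 + 0.0415)/110] = 0.0242. (0.06 − 0.02)/0.0242 = 1.655, and Φ(0.01) = 0.50; exact 0.53.

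**Year 2, even spread.** The rates are 0.0467 and 0.0867, δ = 0.04, SE = 0.0335. 0.02/0.0335 = 0.597, and Φ(−1.048) = 0.147; exact 0.17.

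**Other time courses**, all reaching 7 % v 13 % at 3 years, 110 per arm. Constant hazard uses 1 − (1 − p)^(t/3). The delayed rows keep the titanium hazard constant and start the excess later.

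| Assumed time course | Year 1 | Year 2 | Year 3 |
|---|---|---|---|
| Even spread | 0.53 | 0.17 | 0.055 |
| Constant hazard (0.024 v 0.045 at year 1) | 0.50 | 0.15 | 0.055 |
| Excess only after 12 months | 0.88 | 0.26 | 0.055 |
| Excess only after 18 months | 0.88 | 0.38 | 0.055 |
| 50 % of recurrences by year 1, 75 % by year 2 | 0.30 | 0.12 | 0.055 |
| 60 %, 85 % | 0.21 | 0.09 | 0.055 |
| 70 %, 90 % | 0.15 | 0.075 | 0.055 |

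The chance of passing at any of the three looks is 0.54 with even spread and 0.51 with constant hazard, nearly all of it from year 1.

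**A device worse than the margin**, constant hazard. A true 3-year rate of 15 % passes 0.37 of the time at year 1 and 0.08 at year 2. A true rate of 20 % passes 0.15 and 0.01.

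**Would an alpha split help?** With 0.05/3 = 0.0167 per look, year 1 is still 0.39 (even spread) or 0.36 (constant hazard). By contrast, three equally spaced unadjusted looks at one and the same quantity would give about 0.10. The 3-year margin applied to early rates is the main driver, more than the unadjusted level.

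**Calendar reading.** If looks are counted from the first enrollment, later patients have shorter follow-up. With uniform accrual, even spread and crude proportions among those enrolled, the year-1 values are:

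| Assumed accrual (years) | 0.5 | 1 | 1.5 | 2 | 3 |
|---|---|---|---|---|---|
| Year-1 pass probability | 0.68 | 0.84 | 0.76 | 0.69 | 0.53 |

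Constant hazard gives 0.51 to 0.82. On this calendar even the third analysis would have 36 months of data on almost no one; its pass probability is about 0.07 to 0.30 over the same accrual range.

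**The case against.** The strongest objection is that the article never says the non-inferiority test is repeated. The endpoint is fixed at 3 years in the abstract, the Background and Outcome parameters. Years 1 and 2 are called only interim evaluations, and the test and level stand next to the sample size calculation. Nothing permits early stopping or an early declaration. If the early looks are descriptive, none of the early pass probabilities applies. Alpha allocation and release rules may also sit in a full protocol or analysis plan that is not shown.

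This stands as a limit on the claim. A reader might infer that the plan tests non-inferiority three times, or that an inferior device would most likely pass early. The documents support neither. Repetition of the test is an inference, and the year-1 probability runs from 0.15 to 0.88 on assumed time courses, with lower year-2 values and lower values for devices clearly beyond the margin. The 0.84 calendar figure is the highest of the accrual periods tried.

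The concern about influence on conduct is also limited. Follow-up is done by a blinded physician, and nothing says that by-arm results reach the surgeons.

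What the objection does not remove is that the article itself ties the early evaluations to the primary endpoint, offers only a 3-year margin, and dates the analyses in two different ways. These are features of the text shown, not details missing from it.

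**Conclusion.** The point holds in conditional form. The plan schedules analyses at years 1, 2 and 3, gives a single one-sided 0.05 level and a single 3-year margin, and does not reserve the non-inferiority conclusion for year 3. If the margin and level were used early, a device exactly at the margin would pass with probability 0.50 to 0.53 at year 1 and 0.15 to 0.17 at year 2 under constant hazard or even spread, instead of 0.055. Across all the per-patient time courses tried, the ranges are 0.15 to 0.88 and about 0.075 to 0.38. On the first-enrollment calendar, year 1 is about 0.53 to 0.84 under even spread.

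These figures assume 110 per arm, no losses, true rates of 7 % and 13 % at 3 years, and the time courses and accrual periods stated. Every scenario at the margin exceeds 0.05 at both early looks, so the direction is not in doubt; the size depends on timing that the article does not give. The sponsor should clarify this before any interim output is produced.

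**What to change.** Amend Outcome parameters and Statistical methods to state that:

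1. The only confirmatory non-inferiority test, at the full one-sided 0.05 with the 6-point margin, is made once, on complete 3-year follow-up of each patient.
2. The 1- and 2-year evaluations are descriptive, and no non-inferiority conclusion is drawn from them.
3. By-arm interim recurrence results stay with the statistician and are not released to operating surgeons or follow-up physicians before the 3-year analysis.
4. The analysis times are defined once. Follow-up per patient (Outcome parameters) and years since the first enrollment (Statistical methods) must be reconciled.

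An alpha-spending rule is not a substitute, because it leaves the 3-year margin in place at looks where it is too wide. The change is wording only: it needs no extra patients and keeps the full 0.05 for year 3. The price is that early by-arm publication of recurrence is given up.

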### Statistical methods

The sample size calculation is based on the primary end point. A sample size of 110 in each group permits the achievement of a study power of 80 %, to detect a non-inferiority margin difference between the devices used. The reference group proportion is 0.07. The treatment group proportion is assumed to be 0.13 under the null hypothesis of inferiority. The statistic test used will be the one-sided Z test (unpooled). The significance level of the test will be targeted at 0.05.

The same sample size will also be adequate to evaluate the secondary endpoints.

Statistical analysis will be performed at 1, 2 and 3 years after the first patient’s enrollment by a statistician affiliated with the Reference Center.

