The Italian Society of Endoscopic Surgery recently carried out a Consensus Conference with a systematic literature search on this topic and concluded that “*mesh fixation with spiral tacks should be considered the standard method of fixation in laparoscopic ventral/incisional hernia repair*” and that “*there is not enough evidence to make any recommendation in favor or against the use of the absorbable fixing devices*” [24]. Also, the International Endohernia Society published its evidence-based guidelines and came to similar conclusions. Both guideline panels found very little literature about the role of absorbable fixing devices and stressed the need for further research about it [25]. In fact, the current evidence on the use, safety and efficacy of absorbable tacks for mesh fixation is still based on few retrospective studies giving inconclusive results [21,22], and a recent report from a National Register [26], which concludes that the use of absorbable tacks is related to an increased risk of hernia recurrence. The latter deals with a very large number of patients but does not provide any information either about the type of mesh or the specific kind of tacks used. The absence of this crucial information limits the usefulness of the study. The direct comparison of absorbable tacks with the current “gold standard,” represented by titanium tacks appears to be the best way to assess their efficacy and safety.

Our study primary objective is to determine if absorbable tacks are non-inferior to titanium tacks for lightweight mesh fixation during LIVHR in the end point of recurrence rate, considering a follow-up of 3 years.

The secondary objectives are to evaluate the possible superiority of the absorbable tacks in improving post-operative stay, complications, pain and comfort.

Our choice of a non-inferiority trial design was based on the assumption that some of the complications related to the use of metal spiral tack could be avoided by the use of absorbable devices if their non-inferiority to the reference treatment (metal tacks) is demonstrated.

This protocol has been prepared in accordance with Standard Protocol Items: Recommendations for Interventional Trials (SPIRIT) [27] and the Consolidated Standards of Reporting Trials (CONSORT 2010) [28], taking into accounts its Extension for Nonpharmacologic Treatment Interventions [29] and the CONSORT Statement for Reporting Noninferiority and Equivalence Trials [30].

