### Study population and eligibility criteria

All consecutive patients referred to the involved surgical units will be checked to determine eligibility, by one dedicated team member, according to the inclusion and exclusion criteria specified in an additional file (see Additional file 1).

All the eligible patients will be consecutively enrolled in the study until the sample size of 220 patients is reached. The included patients will be divided into two groups:Group A: patients submitted to LIVHR by lightweight polypropylene mesh fixed by titanium helicoidal tacks (control group);Group B: patients submitted to LIVHR by lightweight polypropylene mesh fixed by absorbable tacks (study group).

Each patient will be introduced to the trial by a member of the research group and receive an explanation of the study protocol (including random assignment of the fixation device that will be used during surgery). A specific informed consent regarding participation in the trial, randomization and explanation of the laparoscopic hernia repair, with no disclosure about the fixation device will be obtained and signed before enrolling in the study.

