### Randomization, allocation concealment, and blinding

A simple 1:1 allocation ratio randomization (without any restriction) will be guaranteed by an on-line computerized random generator. Patients will be randomly assigned to either Group A or Group B in the operating room, just before surgery.

Patients will be kept blind to the allocation status. Furthermore, post-operative controls will be performed at each center by a physician not directly involved in the study. He will be kept blind to the particular device used on each patient. Due to the nature of the intervention, the operating staff cannot be blinded to allocation but will be instructed not to disclose the allocation status of the participant at any time.

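### The stated 80% power does not follow from the stated inputs: 110 per group gives about 54% at equal 7% recurrence, and 80% only if absorbable tacks are truly better (about 5%)

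*Protocol article*

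**What the plan says.** The Statistical methods section sizes the trial on 3-year recurrence and says "A sample size of 110 in each group permits the achievement of a study power of" 80%. It gives two rates: "The reference group proportion is 0.07", and "The treatment group proportion is assumed to be 0.13 under the null hypothesis of inferiority". The test is a one-sided Z test with unpooled variance, and "The significance level of the test will be targeted at 0.05". Allocation is 1:1 (Randomization, allocation concealment, and blinding).

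No absorbable-tack rate under the alternative is given. On recruitment, the section on study population says "All the eligible patients will be consecutively enrolled in the study until the sample size of 220 patients is reached"; the article mentions no allowance for patients lost over the 3 years.

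**The concern.** The two printed rates fix the margin at 0.13 − 0.07 = 0.06. Power for non-inferiority also depends on the true rate in the new-treatment group, and that is the one value left out. The conventional choice is equal rates, and the Discussion part of the Abstract frames the aim as finding out whether absorbable tacks perform as well as non-absorbable ones. Under that choice, 110 per group looks far too small for 80% power with a 6-point margin.

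If so, a trial of two identical devices would come close to a coin toss. Readers told that power was 80% could take a failure to show non-inferiority as evidence against absorbable tacks, when it may only reflect the trial's size. The article's Discussion links encouragement of the new device to this result.

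**Working it through.** **Inputs, all from Statistical methods except the last**

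- n = 110 per group
- titanium rate p_C = 0.07
- margin M = 0.13 − 0.07 = 0.06
- one-sided alpha 0.05, z = 1.645; 80% power, z = 0.842
- true absorbable rate p_T: not stated, so varied below

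**Formula (unpooled normal approximation)**

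SE = sqrt{[p_C(1 − p_C) + p_T(1 − p_T)] / n}

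Power = Φ{[M − (p_T − p_C)] / SE − 1.645}

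**Attempt to reproduce 80% at equal rates, p_T = 0.07**

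- SE = sqrt(2 × 0.07 × 0.93 / 110) = 0.0344
- Power = Φ(0.06 / 0.0344 − 1.645) = Φ(0.099) = 54%
- Full enumeration of the binomial outcomes for the same test gives 54.8%.
- Size needed for 80%: (1.645 + 0.842)² × 2 × 0.07 × 0.93 / 0.06² = 223.6, so 224 per group (448 in total).

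**Other readings, at 110 per group and one-sided 0.05**

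- variance taken under the null: 43% to 44%
- continuity correction: 43%
- one-sided superiority power for 7% against 13%: 44%
- arcsine scale: 44%
- log risk ratio: 35%; log odds ratio: 36%
- 0.13 read as the margin itself: 98%

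Relaxing alpha to one-sided 0.10 at equal rates gives 68%. None of these returns 80%.

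**Solving for the true rate that gives 80%**

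Setting power to 0.80 at n = 110 gives p_T = 0.0503. Check at 5%:

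- SE = sqrt[(0.0651 + 0.0475) / 110] = 0.0320
- Power = Φ(0.08 / 0.0320 − 1.645) = 80.4%
- Size needed for 80%: 6.18 × 0.1126 / 0.08² ≈ 108.8, so 109 per group

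**Power by true absorbable-tack rate, 110 per group**

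| True rate | Power |
|---|---|
| 5% | 80% |
| 6% | 68% |
| 7% (equal) | 54% |
| 8% | 41% |
| 9% | 29% |

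**Loss to follow-up (assumed rates, equal 7%)**

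- 10% loss, 99 per group: SE = 0.0363, power 50%
- 20% loss, 88 per group: SE = 0.0385, power 47%

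**The case against.** The strongest reply is that power cannot be shown wrong without the alternative rate, and the article does not give it. The 54% rests on an equal-rates assumption supplied by the reader. A true rate of 5% reproduces the design almost exactly (109 per group required), so the sponsor may have entered 5% and calculated correctly. A journal article is also a condensed account, and the full protocol may state the rate.

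The first part stands: 5% may well be what was used, and the error may be an undisclosed assumption and not a slip in calculation. It does not rescue the sentence. The article prints every other input and then claims a power that those inputs do not deliver under the ordinary reading. If 5% was used, the 80% depends on absorbable tacks being truly better by 2 points, and nothing in the article supports that. The advantages it hopes for are in pain, comfort, complications and stay, and the studies it cites found similar outcomes.

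The Background also cites a register report that "concludes that the use of absorbable tacks is related to an increased risk of hernia recurrence". The article discounts that report because it lacks detail on the mesh and tacks, so it carries limited weight here.

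Two further points are fairly made against pressing too far. The planned total of 220 lies close to the 224 needed per group (220 per group would give 79.4%), but a confusion of total with per-group size is conjecture and the finding does not need it. A dropout allowance may be in the full protocol; the loss figures above are assumed and secondary.

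**Conclusion.** The statement is wrong as written. With a 7% reference rate, a 6-point margin, one-sided alpha 0.05 and 110 evaluable patients per group, power is about 54% when the devices are equal. The chance of failing to show non-inferiority is then about 46%, where a reader would expect 20%. The claimed 80% holds only at a true absorbable-tack rate of about 5%, which the article does not state. The conclusion rests on the printed inputs and on equal rates as the natural premise of a non-inferiority comparison; the figures for loss to follow-up are illustrative. Because this is the power claim for the primary endpoint, it must be corrected.

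**What to change.** State which true absorbable-tack rate was used and why, then replace the power sentence with wording such as:

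> With 110 evaluable patients per group, a margin of 0.06 (0.13 minus 0.07), one-sided alpha 0.05 and true recurrence of 7% in both groups, power is about 54%; 80% holds only if the true absorbable-tack rate is about 5%.

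This wording is true whichever rate was entered. Add the power expected after the anticipated 3-year loss to follow-up.

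The cost is protocol wording only: no extra patients are needed, and the stated power becomes less favourable. Restating the power discloses the shortfall but does not remove it. For information, 80% at equal rates would need 224 evaluable patients per group.

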There will be no difference in preoperative or post-operative care between the two groups. All patients will receive 1 dose (1 g) of paracetamol given intravenously at surgery and 2 more, each at 8-hour interval. Additional need for pain management will be noted on the records. The follow-up will be scheduled as follows:1 week (clinical evaluation)4 weeks (clinical evaluation)6 months (clinical evaluation or phone interview)12 months (phone call and eventual clinical evaluation)24 months after surgery (phone call and eventual clinical evaluation)36 months after surgery (phone call and eventual clinical evaluation)

During the follow-up, hernia recurrence (with eventual imaging studies) and post-operative complications will be checked. The following data will be also evaluated, using the licensed Carolinas Comfort Scale (CCS) [34,35]:Pain (during resting, during daily activities, during walking, during exercise):Pain control by use of analgesic drugs (which kind of drug, which dosage)Pain at physical examination

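### The 3-year recurrence comparison is a Z test on crude proportions, so once patients are lost its bias and power depend on the denominator; a 36-month Kaplan-Meier difference is safer

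*Protocol article*

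**What the plan says.** The Outcome parameters section of the protocol article defines the primary measure: "The endpoint will be measured by the recurrence rate at 3 years". The Statistical methods section gives the design values, "The reference group proportion is 0.07" and "The treatment group proportion is assumed to be 0.13 under the null hypothesis of inferiority", and then the test: "The statistic test used will be the one-sided Z test (unpooled"). The level follows: "The significance level of the test will be targeted at 0.05". The test sentence stands in the sample-size paragraph, but it is worded prospectively and is the only test of the primary endpoint in the article.

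The follow-up list in the section on intervention and management puts contacts at 1 and 4 weeks and at 6, 12, 24 and 36 months. The contacts from month 12 on are telephone-first. The last one reads "36 months after surgery (phone call and eventual clinical evaluation"). The Statistical methods section also dates the analyses at 1, 2 and 3 years, counted from the entry of the first patient.

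**The concern.** A two-proportion test needs a 36-month status for every patient in its denominator. Someone last assessed at month 12 or 24 without recurrence has no such status. An analyst holding to the named test must count that patient as recurrence-free, drop the patient while keeping those who recurred before loss, or restrict the analysis to patients followed to month 36. The three choices give different answers.

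The direction matters because non-inferiority is the sole primary claim. Counting losses as recurrence-free shrinks both rates and the gap between them, which makes non-inferiority easier to declare. The other two choices discard information in a trial whose power is already below what it states.

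**Working it through.** **Inputs from the article.** n = 110 per arm; reference rate 0.07; rate under the null 0.13; hence margin 0.13 − 0.07 = 0.06; one-sided 0.05 (z = 1.645).

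**Assumed, because the article gives none.** Constant recurrence hazard; constant loss hazard independent of recurrence; 10% to 30% lost by month 36; for power, a true rate of 7% in both arms.

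**The plan's own figure.** "A sample size of 110 in each group permits the achievement of a study power of 80" per cent. With no loss, SE = √(2 × 0.07 × 0.93 / 110) = 0.0344, and power = Φ(0.06/0.0344 − 1.645) = 53.9%. At equal 7% rates, 80% needs (1.645 + 0.842)² × 2 × 0.07 × 0.93 / 0.06² ≈ 224 per arm. The stated power is therefore not reproduced, before any loss is considered.

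**Closed form at 20% loss in both arms.** Let λ = −ln(1 − p) and μ = −ln(1 − 0.20) = 0.2231 per 36 months. The share seen to recur before loss is F = λ/(λ + μ) × [1 − (1 − p) × 0.80].

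- p = 0.07: λ = 0.0726, F = 0.2454 × 0.256 = 6.3%.
- p = 0.13: λ = 0.1393, F = 0.3843 × 0.304 = 11.7%.

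*Lost counted as recurrence-free.* The difference is 11.7 − 6.3 = 5.4 points instead of 6.0. SE = √[(0.0628 × 0.9372 + 0.1168 × 0.8832)/110] = 0.0384. False non-inferiority = Φ((0.06 − 0.054)/0.0384 − 1.645) = 6.8%. At 10% and 30% loss it is 5.8% and 8.1%.

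*Early recurrences plus completers.* The rates become 0.0628/(0.0628 + 0.93 × 0.80) = 7.8% and 0.1168/(0.1168 + 0.87 × 0.80) = 14.4%, a difference of 6.6 points. At equal 7% rates about 88.75 patients per arm remain, SE = 0.0402, and power = 43.9%.

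*36-month completers only.* The rates stay at 7% and 13%. With 110 × 0.80 = 88 per arm, SE = √(2 × 0.0651/88) = 0.0385 and power = 46.6%.

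*Kaplan-Meier.* The rates stay at 7% and 13%. Variance per arm = 0.93² × 0.2454 × [1/(0.93 × 0.80) − 1]/110 = 0.000664, so the SE of the difference is 0.0364 and power = 50.1%. At 30% loss the closed-form powers are 42.6% for completers and 47.8% for Kaplan-Meier.

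**Simulation.** The closed form assumes that recurrence is detected continuously. Simulating detection only at the scheduled contacts, with 110 per arm, gives the results below. A range means that separate runs differed slightly.

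| Rule | Mean difference, 20%/20% loss (true 6.0) | False non-inferiority, 20%/20% | False non-inferiority, 10% titanium / 25% absorbable | Power at 7% v 7%, 20%/20% |
|---|---|---|---|---|
| Lost = recurrence-free | 5.25 | 7.9–8.6% | 11.9–12.4% | not relevant |
| Early recurrences + completers | 6.4 | 4.4%* | 3.3–3.4% | 46.8% |
| 36-month completers | 5.95 | 5.9% | 5.8–6.2% | 48.7% |
| Kaplan-Meier, Greenwood SE | 5.95 | 5.5–6.0% | about 6% | 50.7–51.2% |

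*Continuous detection.

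With no loss every rule coincides, and simulated false non-inferiority was 5.7%. About 0.7 points above nominal therefore belong to the unpooled test at this sample size, not to loss. On the contact schedule the completers' power deficit against Kaplan-Meier is about 2 to 4 points at 20% to 30% loss. The closed form puts it higher (3.5 and 5.2 points) because it credits observation between contacts.

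**Timing.** If the final analysis falls 3 years after the first patient enters, almost nobody has had the 36-month contact and the curve effectively stops at month 24. It then estimates 1 − 0.93^(24/36) = 4.7% and 1 − 0.87^(24/36) = 8.9%, a gap of 4.2 points where the truth is 6.0. With assumed uniform accrual over 12 or 24 months and no loss, simulated false non-inferiority by Kaplan-Meier is about 15%.

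**The case against.** The strongest case against has five parts.

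- **No denominator is fixed.** The article names a test and no rule for lost patients. A condensed article may leave that to the full protocol or analysis plan. This stands. A reader might infer that lost patients will be counted as recurrence-free, but nothing says so, and the 8% and 12% figures describe only what happens if that rule is chosen. The point rests on the named method, not on a missing rule.
- **A crude comparison can be unbiased.** This also stands. It is tempting to say that no crude denominator is right, but the completers-only rule is unbiased under the same non-informative-loss assumption that Kaplan-Meier needs, and its error rate is about the same. It does discard recurrences already recorded in patients later lost, and some power.
- **The power gain is small.** True: about 2 points over completers at 20% loss. Kaplan-Meier does not avoid the power loss; by the closed form, power still falls from 53.9% to 50.1%.
- **The loss rates are assumed, and unequal loss is unsupported.** Correct. Patients and the assessing physicians are to be blinded, and nothing suggests more loss on absorbable tacks. The 10% v 25% case shows sensitivity and is not a forecast.
- **Early recurrences plus completers errs conservatively.** Also correct: its false non-inferiority falls below 5%. Its cost is overstated rates and lost power.

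What survives is that the only named test gives materially different answers under plausible denominators, one of which favours the claim, and that a method using all observed follow-up is available at little cost.

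**Conclusion.** The concern holds in a limited form. With loss over 36 months, the named Z test is anti-conservative, or overstates both rates and loses power, or is unbiased with a modest loss of power, depending on the denominator. At an assumed 20% loss in both arms the range is about 8% false non-inferiority at one end and about 47% power at the other. Kaplan-Meier gives about 5.5% to 6% and 51%. With little loss the differences are small, and with none they vanish.

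Kaplan-Meier removes the bias only if loss is unrelated to recurrence. It recovers part of the lost power, cannot recover recurrences missed on the telephone, and does not help if the final analysis is timed from the first enrolment. The shortfall of about 54% power against the stated 80%, at equal true rates of 7%, is a separate matter that no change of estimator repairs. The change is worth making, but the point does not show that the trial as planned would reach a wrong conclusion.

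**What to change.** Replace the test sentence with: *The primary analysis is the difference (absorbable minus titanium) in 36-month cumulative recurrence estimated by Kaplan-Meier, with patients censored at the last contact at which recurrence was assessed and Greenwood standard errors. Non-inferiority is shown if the upper one-sided 95% limit is below 6 percentage points. The analysis is performed after the last randomized patient's 36-month contact.* Keep the Z test on observed proportions as a sensitivity analysis, with its denominator stated.

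The cost is a few lines of text. The data needed are the date of recurrence and the date of last assessment, which the existing contact schedule yields. The final analysis would come later than 3 years after the first enrolment, by about the length of accrual. Two limits remain and should be acknowledged: recurrence is dated only to the nearest contact, and loss is assumed to be non-informative, as it also is under completers-only.
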